## Results

The study has started in January 2021. Funding was completed in March 2022. The first participant was enrolled in May 2023. As of June 2025, we have enrolled 6 patients in phase 1 and 3 patients in phase 2. No data analysis has been done yet. We expect data collection to be completed and published in 2028.

## Discussion

### Anticipated Findings

A literature review [9] on cervical ITB suggests improvement of UE spasticity and function, without causing more complications than thoracolumbar ITB. However, the data prevent definite conclusions. In 2024, a retrospective case series by Mossner et al [10] was performed in children with hypertonia, highlighting the safety and efficacy of using cervical ITB. They concluded that the cervical catheter tip location for ITB was safe, was effective in controlling tone, and should be considered for the treatment of hypertonia. Larger studies with longer follow-up were suggested to further determine upper-limit dosing safety, along with long-term functional benefits in these patients. This study will be the first study that will investigate whether cervical administration of ITB is safe in adults with SCI.

In addition to safety, efficacy will be exploratively assessed before phase 1 and at 3, 6, and 12 months after implantation of the ITB pump. The intermediate and long-term effects of cervical administration of ITB on respiratory muscles affecting pulmonary functions and SAS, as well as the effects of decreasing spasticity of the UE and LE on participants’ satisfaction, function, activities, and participation, will be assessed.

Besides the aforementioned direct effect of reduction of spasticity on UE function, reduction of spasticity may have an additional indirect benefit on UE function. At the end of conventional rehabilitation, UE reconstructive surgery is a well-documented and effective treatment in tetraplegia to improve arm or hand function [39]. Spasticity may adversely affect the outcome of this surgery and is mostly considered as a contraindication and must be treated first [40,41]. In case of generalized spasticity, cervical ITB may enable UE reconstructive surgery and thereby indirectly improve UE function.

When cervical ITB seems to be both safe and effective, it will change the usual care of this treatment. The catheter tip position should then be dependent on the localization of spasticity and treatment goals: tip at thoracolumbar level for functionally hindering spasticity of the LE muscles and tip at cervical level for functionally hindering spasticity of UE and LE muscles.

### Limitations

This study protocol has some limitations. Although the safety aim of the study is clear, it is important to note that this study is not powered to test for efficacy. It will provide us with the first exploratory data on efficacy, which can be used to power a subsequent study on efficacy. In addition, we anticipate variation in catheter placement relative to the lesion level. Although the catheter tip will deliberately be positioned just below the lesion to maximize sympathetic activity reduction, its proximity to the diaphragm may impact diaphragmatic function and, consequently, safety and efficacy. This variability will be considered when interpreting the results.

Although spasticity is a common complication in all central nervous system disorders with involvement of the upper motor neuron, only adults with SCI in a chronic phase will be included in this study. A potential follow-up study, in which adults with other disorders of the upper motor neuron and adults within 1 year after the onset of SCI can also be included, will focus more on effectiveness. However, the intensity of the current protocol may impact participants’ adherence and study feasibility, particularly in larger-scale or multicenter settings. Therefore, in this study, we will evaluate whether the frequency and scope of the postimplantation assessments can be reduced without compromising data quality or participant safety.

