### Sample Size

No sample size calculation was performed for this pilot safety study. On the basis of a previous comparable study by Bensmail et al [3] with 11 participants, we decided to include the same number of participants. We expect that we need to screen and recruit 25 participants to retain 11 participants at the start of the phase 1 because of the safety criteria for inclusion (Figure 1).

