### Statistical Analysis

Because of the small sample size, it is expected that the continuous variables will not be parametrically distributed; therefore, they will be presented as median with IQR. Furthermore, due to the small sample size, pre- and postassessments during the first phase or the ITB trial phase will be compared with descriptive statistics and differences will not be formally tested. In addition, the measurements in the second phase after definitive implantation of the baclofen pump (3, 6, and 12 months after implantation) will be compared with descriptive statistics. Changes over time in the outcome measures within patients will be visually explored.

For categorical variables, we will present numbers and corresponding percentages. To compare pre- and postassessment during the first phase or the ITB trial, cross tabs will be made. Our primary analysis population is the intention-to-treat analysis. Considering the study design, we expect a few missing data. In case of missing data, we will use generalized estimation equations analysis (<20% missing data) or multiple imputations (>20% missing data).

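### Median with IQR is justified by a wrong argument from sample size, and the stated outputs give no numerical estimate or SD of within-person change

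*Protocol article*

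**What the plan says.** The Statistical Analysis section opens with its reason: "Because of the small sample size, it is expected that the continuous variables will not be parametrically distributed". The consequence follows directly: "therefore, they will be presented as median with IQR". No other reason is given, and no distinction is made between one continuous outcome and another.

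Phase 1 pre- and post-assessments are compared descriptively, and "differences will not be formally tested". The 3-, 6- and 12-month measurements are also compared descriptively. On change within a person, the plan says: "Changes over time in the outcome measures within patients will be visually explored". A model appears only as a response to missing data: "we will use generalized estimation equations analysis (<20% missing data) or multiple imputations (>20% missing data").

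The Limitations section says the study is not powered for efficacy, and adds: "It will provide us with the first exploratory data on efficacy, which can be used to power a subsequent study on efficacy". It calls the follow-up study a possibility. On numbers, the Sample Size section says: "We expect that we need to screen and recruit 25 participants to retain 11 participants at the start of the phase 1". It states that no calculation was made.

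**The concern.** There are two separate problems.

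1. **The premise is wrong.** A variable such as PcCO2 or forced vital capacity has the same distribution in the population whether 11 or 1,100 people are measured. A small sample makes that distribution hard to check. This can be a reason for caution, but it is not evidence of non-normality. Median and IQR may suit some of these outcomes, but the reason would be the outcome's scale or its skew.

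2. **The stated outputs do not match the stated use.** The design is single-arm and pre-post, so the natural quantity is each person's own change. The named outputs are medians and IQRs, plus plots. They include no numerical estimate of paired change, no interval and no SD of change. Medians and IQRs by visit do not yield the SD of change, because that also depends on the correlation between visits.

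At stake is how useful the published results are to whoever plans the next study. The safety decisions are not affected: the phase 1 stopping rules apply to individual participants.

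**Working it through.** **The plan's own figure.** The 11 participants were taken over from a previous comparable study. No alpha, power, effect size or SD is stated, so there is no calculation to reproduce.

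**Step 1: precision of the median against the mean.** Inputs: n = 11 at the start of phase 1 (Sample Size). The distributional shapes are assumed, because the article gives no distributional data. Simulation, 400,000 samples per setting; efficiency = Var(mean) / Var(median):

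| Assumed shape | n | Var(mean) / Var(median) |
|---|---|---|
| Normal | 11 | 0.66 |
| Normal | 6 | 0.78 |
| Laplace | 11 | 1.3 |
| t, 3 df | 11 | 1.5 |
| Lognormal, sigma 1 | 11 | 2.5 |

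Under normality at n = 11 the loss is 1 - 0.66 = 0.34, about one third. For the last three shapes the median is the less variable summary. (In the lognormal case the mean and median also estimate different quantities.)

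**Step 2: spread from an IQR.** Under normality at n = 11, IQR/1.349 estimates the SD with a coefficient of variation of 33%, against 23% for the sample SD. With the quartile convention used it averages 0.88 of the true SD, about 12% low. So even a reported IQR of change would give only a rough SD.

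**Step 3: why visit-wise spread is not enough.** With equal variance at both visits,

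SD(change) = SD(visit) × √(2(1 - r)).

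For illustration, assume a two-arm trial comparing change, two-sided alpha 0.05, 80% power and a difference of 0.5 baseline SD:

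n per arm = 2 × (1.96 + 0.84)² × 2(1 - r) / 0.5² ≈ 62.8 × 2(1 - r).

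| r | 2(1 - r) | n per arm |
|---|---|---|
| 0 | 2.0 | 126 |
| 0.3 | 1.4 | 88 |
| 0.5 | 1.0 | 63 |
| 0.7 | 0.6 | 38 |
| 0.9 | 0.2 | 13 |

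The same visit-wise SD is compatible with every row. The row is fixed only by r, or by the SD of change itself.

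**Step 4: what adding the SD would deliver.** The 95% CI for an SD runs from √((n - 1)/χ²(0.975)) to √((n - 1)/χ²(0.025)) times the estimate. At n = 11 that is 0.70 to 1.75. Squared, the later sample size ranges from 0.49 to 3.08 times its planned value, for example 31 to 194 per arm around 63. At n = 6 the multiplier is 0.39 to 6.0.

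**Step 5: which changes can be formed.** Table 1 schedules capillary blood gas and spirometry at screening (T0A1), T0A2, T1 and T2 to T4. Grip and pinch strength, range of motion and walking tests are scheduled at screening and T2 to T4 only. Pulse oximetry has no entry at T0A2 or T1. A T1 change is therefore available for PcCO2 and spirometry, but not for strength, range of motion or walking.

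**The case against.** The strongest reply is that median with IQR is a defensible description of 11 people, and that the Limitations sentence speaks of data, which is more than published summaries. Coded participant data are kept for 10 years (Ethical Considerations), so the sponsor can compute an SD of change whenever it wishes. This stands. A reader might infer that the plan cannot supply the SD, or that it breaks a promise. The documents do not support either: the article says only that the data can be used in this way, and describes the follow-up as potential.

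It can also be said that the main efficacy scales are not continuous. MAS, PRPM and MRC are ordinal and the PGIC is a 7-point rating. PcCO2 and spirometry are listed as primary safety outcomes. This stands and narrows the point to truly continuous outcomes. Those still include grip and pinch strength, range of motion and walking times.

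A further reply is that a condensed article may leave extra table columns to an analysis plan that is not shown, and that generalized estimating equations are already named. The first part limits how hard the absence of an SD can be pressed. It does not excuse the small-sample argument, which is an affirmative statement. The second part applies only when data are missing, and is not a general estimate of change.

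Finally, an SD from so few people is a weak planning input (Step 4). That is correct, and is a reason to show it with its interval.

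**Conclusion.** The point holds as a minor finding. The small-sample rationale is wrong as written. As stated, the outputs contain no numerical paired-change estimate and no SD of change, although the article names a use that would need one for a continuous endpoint.

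Two stronger conclusions should not be drawn. The first is that the plan throws away a third of its precision. That figure assumes normality at n = 11; it is about 22% at n = 6 (1 - 0.78), which matters because only participants with a safe and positive trial reach phase 2; and it reverses under marked skew or heavy tails. The second is that a later trial would be mis-sized five-fold. The factor 2(1 - r) reaches 0.2 only at r = 0.9, and it does harm only if a planner substitutes visit-wise spread for the SD of change. Nothing in the article proposes that.

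The number of participants and the safety rules are unaffected.

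**What to change.** In Statistical Analysis:

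- Delete the argument from small sample size, and justify median and IQR by outcome scale or observed skew.
- For truly continuous outcomes, report beside the median and IQR the mean and SD of within-person change, with a 95% CI, and the pre-post correlation. Give the SD its own interval.
- Form the changes where Table 1 allows: T1 minus T0A2 for PcCO2 and spirometry; T2, T3 and T4 minus screening for PcCO2, spirometry, grip and pinch strength, range of motion and, if not clearly skewed, walking times.
- Keep median and IQR, or counts, for the ordinal scales.

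The intervals are for estimation, so the decision not to test formally can stand. The cost is one or two sentences and a few table columns. Means need care where data are skewed, and the SD stays imprecise at 11 or fewer. No new measurements are needed. The Results section reports 6 participants in phase 1 and 3 in phase 2 by June 2025 with no analysis done, so the change can still be made before any results are seen.

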## Methods

### Study Design

This multiphase single-arm intervention study will contain 2 phases. We will first start with screening and recruitment to determine if there is an indication for, and if it is safe to start treatment with ITB. Phase 1 will be the safety phase, in which an extracorporeal pump will be used to investigate whether cervically administered ITB leads to reduction of spasticity without adverse effect on pulmonary function and sleep-related disorders. In case of a safe and positive test, we will continue to the next phase (phase 2) in which a baclofen pump is implanted. After implantation, the dosage of ITB will be slowly increased to the optimal setting, and if the participant uses oral spasmolytics, these are phased out. The optimal setting varies in accordance with patient conditions. In this phase of the study, we will focus, in addition to pulmonary function and sleep-related disorders, on the reduction of spasticity; improvement of participants’ level of function, activities, and participation; and participant satisfaction according to the International Classification of Functioning [11].

All participants will be assessed once before the start of phase 1 (T0A1), at the start of phase 1 (T0A2), and daily during phase 1 (T0B). In the case of a safe and positive test, participants will be assessed at the end of phase 1 (T1). During phase 2, they will be assessed at 3, 6, and 12 months (T2, T3, and T4) after baclofen pump implantation. We chose to start the assessment in phase 2 only after 3 months following the implantation because in the first 3 months, the pump settings will still be regularly adjusted to optimize the daily dosage of ITB.

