Daily capillary blood gas samples will be taken, and continuous pulse oximetry during sleep, by use of the OSAsense, will be recorded. If the participant is set on a continuous positive airway pressure (CPAP) device, the CPAP device is read out. The trial will be determined as unsafe and will be stopped if the P_c_CO_2_ is >6.5 kPa for 2 days in a row, according to hypoventilation rules in adults as mentioned by Berry et al [28]. The trial will also be stopped when participants without SAS, during the trial, will develop complaints matching SAS and the Oxygen Desaturation Index (ODI) is between 5 and 15 [27]. The ODI represents the number of desaturations per hour.

A third reason to stop the trial is when participants during the trial have no complaints matching SAS, but the ODI is >15 [27]. If the participant uses a CPAP device, the setting of the device may be adjusted to stay within the safety margin. This safety margin is set at an AHI <5 [24]. This adjustment will be registered. A fourth reason to stop the study is when, after adjustments of the CPAP device, it is not possible to stay within this safety margin [24]. A fifth reason to stop the study is if there is no effect on spasticity at the maximum dose of ITB (200 µg per day).

If the participant experiences a positive effect of the ITB on their spasticity, with a score between 1 and 3 on the Patient Global Impression of Change (PGIC) [29] without deterioration on functionality (PGIC 5-7) and there is not a clinically relevant deterioration of pulmonary function or SAS, it is considered a safe and positive ITB trial with an indication for intracorporeal pump implantation (phase 2) and treatment with ITB at cervical level. We opted for these cut-off values for assessment of reduction of spasticity according to the algorithm established by the European working group for spasticity in adults [30].

If, during the trial, no effect is observed on spasticity or there is a clinically relevant deterioration of pulmonary function or SAS, the trial will be discontinued. This is considered a negative test in which there is no indication for treatment of spasticity with ITB. The catheter and the subcutaneous infusion port will then be removed (Figure 2)*.*

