#### Secondary Outcome Measures

The secondary objective of the study is to explore the effect of cervical administration of ITB on the reduction of spasticity; intermediate and long-term effects on pulmonary function and SAS; and improvement in the level of participants’ function, activities, and participation [11]. Participant satisfaction will also be considered.

All secondary outcome measures are carried out in RCR at screening and at 3, 6, and 12 months after implantation of the baclofen pump by an experienced and trained physiotherapist and occupational therapist. Spasticity and satisfaction will also be measured during phase 1.

Spasticity is measured by the MAS [19] and PRPM [20]. Spasticity will be measured in the UE and LE. The PRPM is an ordinal scale that measures and describes perceived resistance against passive motion. The scale ranges from 0 (no increase in resistance) to 4 (limb is rigid in flexion or extension). During testing, the patient is in a relaxed position (the position of the patient is documented). The patient is instructed not to assist or oppose the movement. First, the passive range of motion of the joint is tested by slow flexion or extension. Subsequently, perceived resistance is assessed within the entire range with a faster movement, covering the whole range within 1 second. The movement can be repeated a maximum of 2 times (the lowest score is noted).

The MAS measures the increase in muscle tone and assigns a grade of spasticity from a 0 to 4 ordinal scale. A score of 0 signifies normal muscle tone, a score of 1 signifies a slight increase in muscle tone with a slight catch when the limb is moved in flexion and extension, a score of 1^+^ signifies a slight increase in muscle tone with minimal resistance at the end of movement, a score of 2 signifies a more marked increase in muscle tone through the entire movement but the limb is still easy to move, a score of 3 indicates a considerable increase in muscle tone and that passive movement is difficult, and a score of 4 indicates that the limb is rigid in flexion or extension. The position of the patient and the procedure is the same as in the PRPM.

Participant satisfaction will be measured by PGIC [29], which is a 7-point scale ranging from 1 (very much improved) to 7 (very much worse). Using the scale, the participant can rate if the ITB has changed the level and the hindrance of the spasticity according to the situation before cervical administration of ITB.

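### The 3-12 month efficacy data describe only participants who passed the test phase, but the powering statement and the intention-to-treat and missing-data rules do not say so

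*Protocol article*

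**What the plan says.** **Entry to phase 2.** Study Design: "In case of a safe and positive test, we will continue to the next phase (phase 2) in which a baclofen pump is implanted". The section ITB Trial (Phase 1) defines such a test as a score of 1 to 3 on the Patient Global Impression of Change (PGIC) for spasticity, "without deterioration on functionality (PGIC 5-7) and there is not a clinically relevant deterioration of pulmonary function or SAS". After a negative test the catheter and port are taken out.

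**Timing of efficacy.** Anticipated Findings: "efficacy will be exploratively assessed before phase 1 and at 3, 6, and 12 months after implantation of the ITB pump". Secondary Outcome Measures: "All secondary outcome measures are carried out in RCR at screening and at 3, 6, and 12 months after implantation of the baclofen pump". That section adds phase 1 measurement for spasticity and satisfaction only. Table 1 agrees: pinch and grip strength, muscle power, passive range of motion, walking, the Canadian Occupational Performance Measure (COPM), the Grasp and Release Test (GRT) and the Quadriplegia Index of Function short form (QIF-sf) are ticked at screening and at T2, T3 and T4 (3, 6 and 12 months after implantation), and nowhere else.

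**Intended use.** Limitations says the study is not powered for efficacy and yields first exploratory data, "which can be used to power a subsequent study on efficacy".

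**Analysis rules.** Statistical Analysis names intention-to-treat as the primary population, plans descriptive summaries without formal tests and expects few missing data. It prescribes generalised estimating equations below 20% missing and multiple imputation above 20%.

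**Progress.** Results, as of June 2025: "we have enrolled 6 patients in phase 1 and 3 patients in phase 2".

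**The concern.** Everyone who contributes a T2-T4 value has already reported improvement in spasticity, has not lost function and has kept acceptable respiratory and sleep findings. The summary at those visits is therefore an effect among people selected on early response. PGIC is both part of the selection rule and an outcome at T2-T4, so for that outcome participants are selected on the scale later summarised as benefit.

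This bias has a known, favourable direction, unlike the random imprecision that any study of 11 people carries. Limitations discusses catheter position, the study population and the burden of assessments, but not this selection. A planner who took the T2-T4 effect at face value for a trial that randomises before the test would expect the responders' effect and see a diluted one.

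The analysis rules add to the difficulty. Starters without a pump have no T2-T4 visits, and the plan does not say whether they fall outside the summary or count as missing.

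**Working it through.** **1. Is there a figure in the plan to reproduce?** No. Sample Size states that no calculation was done. The 11 starters are taken over from an earlier comparable study, and no effect size, SD, alpha or power is given.

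**2. Do the analysis rules fit T2-T4?** There are two ways to treat starters who are not implanted:

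- *Left out.* The summary covers implanted participants only and is not intention-to-treat.
- *Counted as missing.* With 11 starters, 2 without a pump is 2/11 = 18%, under the 20% line, so estimating equations apply. Three without a pump is 3/11 = 27%, over the line, so multiple imputation applies. All observed T2-T4 values come from implanted responders, so imputation would assign the responders' course to people whose catheter was removed.

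Neither reading gives a valid effect in all starters. The expectation of few missing data suggests the first, but the text does not say so.

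**3. How large could the dilution be?** Let p be the share of starters implanted and d the standardised effect among them. Assume no effect in the others and an equal SD. The effect in all starters is p × d. Sample size varies with 1/effect², so the required number is multiplied by 1/p²:

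- p = 0.75: 1/0.5625 = 1.78
- p = 7/11: 121/49 = 2.47
- p = 0.5: 1/0.25 = 4

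The first two shares are assumptions. The only related count is 3 of 6. It is a progress figure, the other three may still be in phase 1, and its exact 95% interval is 12% to 88%. It does not determine p.

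**4. What does this mean for power?** Assumed: two-sided alpha 0.05, 80% power, two equal arms, SD 1, d = 0.5.

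Per arm, n = 2 × (1.960 + 0.842)² / d² = 15.70 / 0.25 = 62.8, so 63.

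If the trial does not select by the test, the effect is d × [p + (1 − p) × f], where f is the fraction of the effect that the others obtain:

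| p | f = 0: needed per arm | f = 0: power with 63 | f = 1/4: needed per arm | f = 1/4: power with 63 |
|---|---|---|---|---|
| 0.5 | 252 | 29% | 161 | 42% |
| 0.7 | 129 | 50% | 105 | 59% |
| 0.8 | 99 | 61% | 87 | 67% |
| 0.9 | 78 | 71% | 74 | 74% |

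The equal-SD assumption matters little: allowing for the extra spread of a mixed group at p = 0.5, f = 0 gives 260 instead of 252. If the next trial randomises after the same test, p = 1 and 63 per arm stands.

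**The case against.** The strongest reply is that the test phase belongs to the treatment pathway. The protocol places it before definitive treatment and treats a negative result as no indication for intrathecal baclofen. On that pathway the effect after a positive test is a legitimate target, and a successor that keeps it is sized correctly. This stands, and it makes the undersizing conditional.

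A reader might infer that the next trial will drop the selection, because the follow-up study sketched in Limitations has a wider population. The documents do not support that: the widening is by diagnosis and time since injury, and nothing is said about when participants would be randomised.

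A reader might also infer that the intention-to-treat label claims a 12-month benefit in everyone who starts. It does not. The primary safety question is set before and during phase 1, where all starters are observed, and the later effects are secondary and descriptive. What remains is narrower: the stated population and missing-data rules do not fit T2-T4.

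Finally, the share passing the test will be known from phase 1, and spasticity and PGIC are recorded there in all starters. So the dilution factor will be available. But those are short-term test data without any of the functional outcomes, and the article does not tell the user of the efficacy data to apply the factor. Table layout can be left to an analysis plan. An unqualified powering statement and a rule that would impute from responders are in the article's own text.

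**Conclusion.** The point holds in a limited form. The T2-T4 efficacy data are conditional on a safe and positive test, the powering statement omits that condition, and the intention-to-treat and missing-data rules cannot be applied sensibly to those visits as written. The primary safety assessment in phase 1 is not affected.

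The size is illustrative only. With p between 0.5 and 0.9 and d = 0.5, a trial sized on the selected effect but randomising before the test would have about 29% to 74% power instead of 80%, depending on what participants without a pump gain. The 4-fold figure should not be read as this trial's expectation, because 3 of 6 cannot fix p. Nor do the documents show that the next trial will be too small: that follows only if it does not select by the same test.

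**What to change.** In Statistical Analysis:

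- Describe T2-T4 changes as effects after a positive test, in implanted participants, against the same participants' screening values.
- State that T2-T4 values are not imputed for participants who were not implanted, and that the missing-data rules apply to visits missed by implanted participants.
- Beside each outcome, give the number implanted and the number improved at 12 months out of all who started infusion, counting those not implanted as not improved. Fix the criterion for improvement in advance for each outcome.

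In Limitations, state that the estimates can size a trial that randomises after the same positive test. A trial that randomises before the test must dilute the effect by the observed share implanted, and with about 11 starters that share will itself be imprecise.

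The cost is wording in two sections and one summary line per outcome. No visit, measurement or clinical rule changes. The downside is that the reported benefit will look less favourable.
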